#### Sensitivity to change analyses on participants outcome data

All outcome analyses will take a sensitivity to change approach. This will include descriptive analyses of the cumulative incidence of depression/anxiety (binary outcome), as well as analyses of change on other outcomes using linear mixed models. All results aim to inform a future definitive trial (event rates and effect sizes, respectively), for outcome selection and sample size calculations.

The primary comparison of interest for the adolescent in a future adequately powered trial is the difference in cumulative incidence rate of depression and anxiety throughout the study until 18 months post-baseline (i.e. proportion of adolescents per arm who score above the depression and/or anxiety cut-off at any one of the follow-up time points). We selected this measurement strategy as it takes into account the episodic nature of depression and anxiety. In addition, a point incidence rate at a single time point, such as 18 months, would miss those who developed depression or anxiety along the way but who are not suffering from either depression and/or anxiety at 18 months post baseline, and would result in lower rates, which will make achieving power for a larger trial more difficult. Exploratory analyses (e.g. based on latent class analysis) can be based on “persistent” depression or anxiety, operationalised as 2 or more time points above cut-off among the T1, T2 and T3 follow-up timepoints. For the pilot trial, we will run descriptive comparisons of cumulative incidence between the arms, while not testing for statistical differences. We hypothesise that the cumulative incidence rate will be higher in the control arm when compared to the intervention arms.

For secondary outcomes of a future adequately powered trial, we will explore the difference in change in each outcome within each trial arm from baseline to each follow-up using linear mixed effects regression models (i.e. assessment of *sensitivity to change*). No formal between group statistical testing will be conducted as this pilot cRCT is not designed to detect effects. Given the small number of clusters (or schools) per arm (*n* = 2), the models will include fixed effects of timepoint and school [74]. For each outcome, we will present the model-predicted means and corresponding 95% confidence intervals for each trial arm and timepoint. 

Following multiple imputation of missing data among participants followed-up, models will each be estimated two times for each outcome in each country. First, following an intent-to-treat principle, we will estimate models including all study participants at all timepoints and according to their randomisation allocation, regardless of attendance. Second, the same models will be estimated but only among the subset of adolescent participants who attended > 70% of the 20 intervention sessions (defined as “completers”). Where possible, models will control for variables included in the random selection of schools (district (Colombia), school size (Nepal) and language (South Africa)). The Benjamini–Hochberg correction will be applied to correct for multiple comparisons.

After analyses are conducted on each of the country-specific data sets, cross-country analyses will be conducted; this may include pooled cross-sectional analyses on the baseline data, or pooled outcome analyses assessing change over time. Models will account for clustering at school level, and random intercepts will be specified for schools and participants to reflect the hierarchical structure of the data. To account for the small number of clusters and likely non-normal distribution of outcomes, we will use a Bayesian multilevel negative binomial or Poisson regression model estimated via Markov Chain Monte Carlo. We will conduct heterogeneity analyses to assess differences in the impact of the intervention across sites, employing interaction effects in regression models on a pooled dataset of all three sites. Analyses will be conducted using Stata, version 16.

The abovementioned sensitivity-to-change analyses will provide input for the expected effect sizes that will be needed for sample size calculations for an adequately powered cRCT, if all criteria for progression to full trial are met (see above). For the same purpose, we will use the baseline data to assess the Intracluster Correlation Coefficient (ICC) due to clustering by school. Additionally, because of interest in targeting adolescents most likely to develop depression or anxiety, we will also descriptively review sensitivity to change with stratification by the IDEA-RS. A detailed statistical analyses plan for all outcomes and potential mediation will be developed, and made openly available, before the end of data collection.

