## Discussion

The aim of the study is to test study procedures and assess the feasibility and acceptability of a new intervention combining self-regulation and economic components to prevent depression and anxiety among adolescents living in urban poverty. Given the bidirectional relationship between poverty and poor mental health, there is a need to generate evidence on the effectiveness of interventions which address both aspects simultaneously. With this study, we expect to meet criteria for progression to full trial that have been established for intervention implementation (i.e. fidelity, retention, adverse events, experience with cash transfers) and trial procedures (i.e. randomisation, masking, data collection, retention, contamination), as well as demonstrating sensitivity to change on all self-report and neuropsychological outcome measures, primarily among participants in the combined intervention arm. From this pilot trial, we will learn whether the interventions, and especially the cash transfer, had any negative impact (e.g. perceived inequity, reduced motivation), and how these can be better mitigated in a future trial. Equally we want to understand whether and how contextual factors might influence aspects of feasibility—especially given the three different study sites (e.g. levels of poverty, gender or cultural factors, across and within the Colombia, Nepal and South African samples). For any of the above findings, we will review if and what changes can be made to address any biases or improve procedures or intervention content.

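### The secondary-outcome models are written without an arm-by-timepoint term, and no between-arm difference in change is specified, although these models are to supply effect sizes for sizing a controlled trial

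*Protocol article*

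**What the plan says.** All of this is in the Protocol article, mainly under Sensitivity to change analyses on participants outcome data.

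- **Target.** For the future trial's secondary outcomes, "we will explore the difference in change in each outcome within each trial arm from baseline to each follow-up using linear mixed effects regression models".
- **Terms.** "Given the small number of clusters (or schools) per arm" (two), "the models will include fixed effects of timepoint and school". No arm term and no arm-by-timepoint term is named for the country models.
- **Output.** For each outcome, "we will present the model-predicted means and corresponding 95% confidence intervals for each trial arm and timepoint".
- **Fits.** Each model is estimated twice per outcome and country. The first fit takes in every participant under the allocated arm; the second is restricted to completers.
- **Covariates.** Where possible, "models will control for variables included in the random selection of schools": district in Colombia, school size in Nepal, language in South Africa.
- **Testing.** "No formal between group statistical testing will be conducted".
- **Use.** The section assigns event rates to the descriptive incidence analysis and effect sizes to the mixed models. It adds that the sensitivity-to-change analyses "will provide input for the expected effect sizes that will be needed for sample size calculations".

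The Discussion expects the study to succeed in "demonstrating sensitivity to change on all self-report and neuropsychological outcome measures, primarily among participants in the combined intervention arm".

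**The concern.** The stated terms and the stated outputs do not fit together. Change by arm, and predicted means by arm and visit, need a model in which arms may change differently. Two main effects fitted to all participants do not allow that. Fitting each arm separately does allow it, but then the only quantity specified is change within an arm.

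A controlled trial is sized on a difference between arms. Change within one arm also contains whatever happens to every participant over 18 months: ageing, the school year, repeated testing. For symptom scores it also contains drift created by the entry screen, because adolescents were enrolled only if they scored below the PHQ-A and GAD-7 cut-offs. If within-arm change is carried forward as the effect size for a secondary outcome, the later calculation rests on the wrong quantity. Under the joint fit, the Discussion's expectation about the combined arm could not be examined at all.

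**Working it through.** **1. Design count.** The target is 8 schools × 30 = 240 adolescents per country, and 4 arms × 60 = 240, which agrees with the Sample size section. No power figure is involved; the point rests on model structure.

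**2. Joint reading, algebra.** With school and timepoint as main effects, the expected score in school *s* at visit *t* is μ + school(s) + time(t). Change from T0 to T3 is time(T3) − time(T0), the same number in every school. Schools are nested in arms, so it is the same in every arm, and the difference in change between any two arms is 0 by construction.

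**3. Parameter count** (8 schools, 4 visits, 4 arms).
- School + timepoint: 1 + 7 + 3 = 11 estimable parameters.
- Adding an arm main effect: still 11, because school determines arm.
- Adding a school-level covariate such as district: still 11, for the same reason.
- Adding arm-by-timepoint: 11 + 3 × 3 = 20. All nine interaction terms are estimable beside school fixed effects.

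**4. Simulated check.** One data set was generated with the design above and a participant random intercept. Assumed, not from the documents: true T0–T3 changes of 0, −0.3, −0.3 and −0.6, and SDs of 0.2 (school), 0.7 (participant) and 0.7 (residual). The total SD is √(0.04 + 0.49 + 0.49) ≈ 1.01, so units are close to SDs.

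| T0–T3 change | Control | Active 1 | Active 2 | Active 3 |
|---|---|---|---|---|
| Raw | +0.192 | −0.273 | −0.285 | −0.686 |
| One joint model, timepoint + school | −0.263 | −0.263 | −0.263 | −0.263 |
| Joint model plus arm-by-timepoint | +0.192 | −0.273 | −0.285 | −0.686 |
| Timepoint + school, separately per arm | +0.192 | −0.273 | −0.285 | −0.686 |

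The joint value is the average of the four raw changes: (0.192 − 0.273 − 0.285 − 0.686)/4 = −0.263. With arm-by-timepoint added, the active-minus-control differences are −0.273 − 0.192 = −0.465, −0.285 − 0.192 = −0.477 and −0.686 − 0.192 = −0.878. Each has a model-based SE of 0.182, so a 95% half-width of 1.96 × 0.182 ≈ 0.36.

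**5. Which reading the text favours.** Two fits per outcome and country, the first on everyone, describes one joint model. The stated target of change within each arm, and the reason given in terms of schools per arm, fit separate models. The article does not decide between them.

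**6. Drift from the entry screen.** If a score is truncated below a cut-off *c* (in SD units) and has retest correlation *r*, its mean later rises by (1 − r) × φ(c)/Φ(c) with no true change. Both inputs are assumptions; the documents give neither.
- c = 1.4 (about 8% screening positive), r = 0.8: 0.2 × 0.163 = 0.033 SD.
- c = 0 (50% screening positive), r = 0.6: 0.4 × 0.798 = 0.319 SD.

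This applies directly only to the screened scores and more weakly to outcomes correlated with them. It also assumes a single truncation at T0. The article describes two screens, and in South Africa some adolescents were enrolled on the Phase 1 screen alone. The part common to all arms cancels in an active-minus-control difference.

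**The case against.** The strongest reply is that the sentence says what the models will include, not that they include nothing else. It explains why school is fixed rather than random, and the sentences around it ask for results by arm. A sensible analyst would fit by arm or add the interaction, and between-arm differences then follow by subtraction. That stands: a reader might infer that the plan forces a zero difference between arms whatever is done, and the documents do not support this. It is true only of the joint fit.

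It is also said that such detail belongs in the statistical analysis plan, which the article promises and which is not shown. This answers only part of the point. The article itself fixes the terms, the outputs and the use of the results, and an analysis plan that copied those terms would inherit the mismatch. The pooled analysis does mention interactions, but for differences across sites, and it does not repair the country models.

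Three further inferences are tempting and not supported:

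- **That the full trial's primary outcome would be mis-sized.** That outcome is cumulative incidence. Its event rates come from the descriptive comparison by arm, outside this model.
- **That the Benjamini–Hochberg step is incoherent because no between-group tests are planned.** It could cover the many within-arm changes, and nothing here requires its removal.
- **That the target difference must come from a minimum important difference.** That is a design preference, not a correction of this plan.

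Abstaining from formal between-group tests is reasonable in a pilot, but it does not remove the need for the estimate.

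**Conclusion.** The point holds for the future trial's secondary outcomes. As written, the country models either force one common change on all four arms, contradicting the promised arm-by-timepoint means, or yield only within-arm change. Under neither reading does the plan specify a between-arm difference in change, although these models are to feed effect sizes into sample size calculations.

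The size depends on the reading. Under the joint fit the estimated difference in change is exactly 0 whatever the data show. Under separate fits nothing is lost in the within-arm estimates, and the gap is the unspecified contrast. The drift of 0.03 to 0.32 SD illustrates why uncontrolled change is a poor input for symptom scores. It rests on assumed retest correlation and screening prevalence and should not be quoted as an estimate for this trial.

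This is a specification to correct before analysis. It does not touch the progression criteria, which are the pilot's primary purpose, and does not warrant the highest severity.

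**What to change.** State the country models as school, timepoint and arm-by-timepoint fixed effects with a participant random intercept. For each outcome, report the change within each arm and each active-minus-control difference in change, with 95% confidence intervals and no p-values. Say that the difference between arms, not the change within an arm, is the effect-size input for secondary outcomes.

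As a minor tidy-up, drop district, school size and language from the country models, where they are redundant beside school fixed effects and do not alter the fit. They can still be used in the pooled models with random school intercepts.

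The cost is wording only, with no new data. The drawback is precision. With two schools per arm the between-arm intervals will be imprecise, and model-based standard errors ignore variation between schools in how much they change. The intervals will therefore tend to look narrower than they should, and the report should say so beside every such estimate.

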
The adolescent assessment will also include heart rate variability (HRV), which is the variation between beat-to-beat intervals. HRV has consistently been shown in meta-analyses to correlate with stress [59], anxiety [60], depression [61] and self-regulation [62]. We will measure 5-min resting state HRV using either a wearable ECG device, the Polar H10 chest strap, which is a well-validated method for measuring HRV [46, 47], or when not feasible, a photoplethysmography (PPG) Bluetooth earlobe device from HeartMath (www.heartmath.com), which has also demonstrated acceptable accuracy at rest [63]. Data will be recorded using the HRV logger application, using a similar procedure as reported by [64]. Since body mass index can explain some of the variance in HRV, weight and height will also be recorded and controlled for [65]. HRV assessments were “resting state” measures, so physical activity was standardised. However, the HRV measures were taken at different times of day, depending on scheduling in schools, so this was not standardised [66].

Finally, three neuropsychological tasks, which have been culturally adapted for the three ALIVE contexts, will also be administered: the Balloon Analogue Risk Task – Youth version (BART-Y) [67], the Emotional Go No-Go Task [68] (in Colombia and South Africa) and the Delay Discounting Task [69]. The BART–Y assesses decision-making and is a computerised measure of risk-taking behaviour balancing the potential for reward versus loss. The original BART includes cash as a reward, which are converted to prizes in the BART-Y. However, several studies have demonstrated that tasks using hypothetical rewards provide valid measures of risk taking [70]. The task will therefore use a points accumulation displayed in the BART-Y, rather than cash or prizes.

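### The cross-country models are fixed as count regressions for all outcomes, although some outcomes are continuous or binary

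*Protocol article*

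**What the plan says.** All statements on the models are in the protocol article, under Sensitivity to change analyses on participants outcome data.

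- **Cross-country models.** After the country-specific work, pooled analyses are described as optional in content: "this may include pooled cross-sectional analyses on the baseline data, or pooled outcome analyses assessing change over time". They have random intercepts for schools and participants. The likelihood is then fixed as a "Bayesian multilevel negative binomial or Poisson regression model estimated via Markov Chain Monte Carlo", for this reason: "To account for the small number of clusters and likely non-normal distribution of outcomes". No other family is named, and the sentence is not restricted to a type of outcome.
- **Country models.** Outcomes other than cumulative incidence are analysed with "linear mixed effects regression models", with predicted means and 95% confidence intervals by arm and timepoint.
- **Cumulative incidence.** The plan is "descriptive analyses of the cumulative incidence of depression/anxiety (binary outcome"), and for the pilot "we will run descriptive comparisons of cumulative incidence between the arms, while not testing for statistical differences".
- **Outcome set.** Under Outcome instruments for adolescents, the measures include "heart rate variability (HRV), which is the variation between beat-to-beat intervals", a delay discounting task, and schooling outcomes such as continued enrolment and dropout. Table 5 lists total PHQ-A and GAD-7 scores.

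The section ends by promising a detailed statistical analysis plan for all outcomes.

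**The concern.** The two reasons given do not lead to a count model. The small number of clusters is addressed by the Bayesian multilevel structure, whatever the likelihood. Non-normality covers skewed continuous, bounded and binary data as well as counts, and each calls for a different likelihood.

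Applied as written, the sentence would put a count likelihood on heart rate variability and on yes/no schooling outcomes. In a Bayesian analysis the width of the posterior follows from the variance that the likelihood assumes, so a wrong mean-variance relation gives wrong intervals. Negative binomial and Poisson regressions also customarily use a log link, so their coefficients are ratios, whereas the country models give differences in means. Results for one outcome could then appear to disagree between the country and pooled analyses because of the scale alone. The section says that the sensitivity-to-change results will feed outcome selection and sample size for the full trial, so the intervals and the scale matter for later use.

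**Working it through.** The article states no figure for the pooled model, so there is nothing to reproduce. Three checks follow. Event rates, means and SDs are assumptions, because the documents give none.

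**1. Binary outcomes (for example enrolment or dropout).** A Bernoulli variable has variance p(1-p). Poisson assumes variance p, and the negative binomial assumes at least that. For the log of one proportion:

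- SE under Poisson = sqrt(1/(np))
- SE under binomial = sqrt((1-p)/(np))
- Ratio = 1/sqrt(1-p)

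This gives 1.05 at p = 0.1, 1.12 at 0.2, 1.20 at 0.3 and 1.29 at 0.4.

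For a log risk ratio between two arms, take n = 628/4 = 157 per arm (628 enrolled, equal split assumed, clustering ignored). With assumed rates of 0.30 and 0.20:

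- Binomial SE = sqrt(0.70/(157×0.30) + 0.80/(157×0.20)) = 0.2008
- Poisson SE = sqrt(1/(157×0.30) + 1/(157×0.20)) = 0.2304
- Ratio = 0.2304/0.2008 = 1.15

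| Assumed rates | Binomial SE | Poisson SE | Ratio | Actual coverage of nominal 95% interval |
|---|---|---|---|---|
| 0.10 / 0.07 | 0.3768 | 0.3933 | 1.04 | 95.9% |
| 0.20 / 0.15 | 0.2481 | 0.2726 | 1.10 | 96.9% |
| 0.30 / 0.20 | 0.2008 | 0.2304 | 1.15 | 97.5% |
| 0.40 / 0.30 | 0.1563 | 0.1928 | 1.23 | 98.4% |
| 0.50 / 0.40 | 0.1262 | 0.1693 | 1.34 | 99.2% |

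The Poisson model can be fitted to 0/1 data and estimates a risk ratio. Its fault is overstated uncertainty, which grows with the event rate.

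**2. Continuous outcomes (heart rate variability).** The Poisson and negative binomial probabilities are exactly zero at non-integer or negative values; evaluation at 3.7, 42.5 and -2.3 returned 0 for both. If software accepts such values anyway, the implied dispersion depends on the units:

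- Assumed mean 42, SD 20: variance/mean = 400/42 = 9.5.
- The same data divided by 1000: 0.0004/0.042 = 0.0095.
- A log-scale measure with assumed mean 3.7, SD 0.5: variance/mean = 0.25/3.7 = 0.07. Neither family allows a variance below the mean. The Poisson SD is sqrt(3.7)/0.5 = 3.85 times the true SD.

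A likelihood whose fit changes with the unit of measurement is not suitable.

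**3. Scale.** Within country, outcomes other than cumulative incidence get linear mixed models and predicted means. In the pooled analysis the same outcomes would get a count model, whose coefficients under the customary log link are log ratios. The article does not say on which scale pooled results will be reported, so a mismatch is possible but not stated.

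**The case against.** The strongest reply has four parts.

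- **The main endpoint is untouched.** A reader might infer that the count model will be applied to the binary depression/anxiety endpoint. The documents do not support this. The section separates cumulative incidence from the modelled outcomes and makes it descriptive, and nothing in the pooled paragraph reverses that. This part of the reply stands in full.
- **The family suits the main symptom scores.** PHQ-A and GAD-7 totals are non-negative integer sums, and participants were selected for scoring below the cut-offs, so low, skewed totals are plausible. A negative binomial model is defensible there, although it ignores the upper bound. This stands too: integer sum scores are not part of the point.
- **The importance is limited.** Pooled outcome analyses are something the plan may include, no formal between-group testing is planned, and the progression criteria do not depend on this model. A reader might infer that the pooled count model is the only source of planning inputs, or that it also governs the site-heterogeneity analysis. The article says neither: planning draws on the sensitivity-to-change analyses generally, and the heterogeneity sentence refers only to regression models on pooled data. This lowers the importance.
- **Likelihoods by outcome belong in the analysis plan.** This would be an answer if the article had left the family open. It did not: it states that a count model will be used, for outcomes in general. A later plan must either follow that sentence or depart from it.

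The reply that a log-link model can also yield predicted means is correct. It shows that the scale problem is avoidable, and the fix uses it.

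**Conclusion.** The point holds in a narrow form. The article fixes a negative binomial or Poisson likelihood for cross-country outcomes without restriction, and the reason given does not justify it for continuous or binary outcomes. For heart rate variability neither family is a proper likelihood. For binary schooling outcomes a Poisson likelihood overstates the standard error by about 5% at p = 0.1 and 20% at p = 0.3; in the two-arm calculation the range is 4% to 34% over assumed control rates of 0.10 to 0.50. These figures rest on assumed event rates, an equal split of 628 adolescents and no allowance for clustering.

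A reader might go further and say that the models cannot be fitted at all. That goes beyond the documents. Poisson can be fitted to 0/1 data, and the article gives neither the units of heart rate variability nor the scoring of the discounting task, so whether negative scores occur is unknown.

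Importance is moderate to low. The sentence should still be corrected, because it is a stated rule that is wrong for some listed outcomes.

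**What to change.** In the analysis plan, with a note that it departs from the article's sentence:

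1. Limit the negative binomial or Poisson model to non-negative integer scores and true counts.
2. Keep the Bayesian multilevel structure with school and participant intercepts, and name a Bernoulli likelihood for binary outcomes and a Gaussian, Student-t or lognormal likelihood for continuous outcomes.
3. Report pooled results also as model-predicted means by arm and timepoint, so that they can be set beside the country models.

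The cost is a change of wording and slightly more analysis work. No data collection or design feature changes.

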### Inclusion and exclusion criteria

The inclusion criteria for adolescents, assessed during Phase 1 were:High levels of multi-dimensional poverty; in Colombia and South Africa this was defined by the geographical catchment area of the selected schools. In Nepal, children attending public schools come from diverse backgrounds; thus, a short screening instrument was used during Phase 1 to identify children living in high levels of poverty in the selected schools before they were enrolled in the cross-sectional survey. This screening instrument is a short tool developed using items from the Global Multidimensional Poverty Index, poverty assessment-related literature, expert consultations and consultations with an Adolescent Advisory Group in Nepal.Aged between 13 and 15 years at the time of Phase 1 recruitment.Fluent in the predominant local language (Spanish in Colombia, Nepali in Nepal and English in South Africa).Screening below validated, country-specific, cut-offs for depression and anxiety on the Patient Health Questionnaire – Adolescent version (PHQ-A) (for depression) [34] and Generalised Anxiety Disorder (GAD-7) (for anxiety) [35] screening instruments.Whose primary caregiver is enrolled in the pilot study (in Colombia and South Africa).

During phase 2, if multiple children in one household fell into the 13–15 years age group, one index child was randomly selected by a member of the research team in each site. In Phase 2, the selected adolescents were screened again using the PHQ-A and GAD-7. Participants who screened *negative* for depression and anxiety were then enrolled in the study; those who screened positive were excluded. When it was not possible to conduct repeat assessments (in South Africa only), adolescents who screened negative on the PHQ-A and GAD-7 during Phase 1 were considered eligible, without a repeat screening assessment before enrolment.

The inclusion criteria for caregivers, defined as the legal guardian living with the adolescent, (assessed during Phase 1) include:Being fluent in the local language (Spanish in Colombia, Nepali in Nepal, and English, Afrikaans or isiXhosa in South Africa).Aged 18 years or more; with their consent to participate in the study.Their child (biological or foster) is enrolled in the study.

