#### Outcome instruments for adolescents

The Patient Health Questionnaire (PHQ-9) Adolescent version (PHQ-A) [34] and Generalised Anxiety Disorder Scale (GAD-7) are the primary outcomes for a future adequately powered trial [35]. They will be assessed using the Measurement of Mental Health among Adolescents and Young People at the Population level Tool (MMAPP) [38], which has the ability to generate equivalency scores for the PHQ-A and the GAD-7. Cut-offs for the PHQ-A and the GAD-7 were previously validated in Nepal, and validations were conducted for Spanish in Colombia and English in South Africa as part of the ALIVE formative work. Based on these validations, cut-off thresholds were selected that minimised false positives. This is because the target group of the intervention is adolescents who do not have depression or anxiety. Sensitivity (and associated false negatives) was less pertinent to selection. (See Table 5 for country-specific cut-offs). The future primary outcome for the full RCT will be defined as the cumulative incidence of depression or anxiety, that is, scoring above depression and/or anxiety cut-offs at one or more of the follow-up assessments.

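### The school ICC for the full trial is to come from baseline data, where the full trial's binary primary outcome is absent by design

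*Protocol article*

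**What the plan says.** All references are to the protocol article.

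- **Source of the ICC.** The section *Sensitivity to change analyses on participants outcome data* says the outcome analyses will supply the "expected effect sizes that will be needed for sample size calculations for an adequately powered cRCT". It then adds, for the same purpose, that "we will use the baseline data to assess the Intracluster Correlation Coefficient (ICC) due to clustering by school". It names no outcome for this ICC.
- **Outcome of the full trial.** *Outcome instruments for adolescents*: "The future primary outcome for the full RCT will be defined as the cumulative incidence of depression or anxiety", meaning "scoring above depression and/or anxiety cut-offs at one or more of the follow-up assessments". The analysis section repeats this as the proportion per arm "who score above the depression and/or anxiety cut-off at any one of the follow-up time points".
- **Who is enrolled.** *Inclusion and exclusion criteria* requires "Screening below validated, country-specific, cut-offs for depression and anxiety on the Patient Health Questionnaire" and on the GAD-7. The Phase 2 re-screen applied the same rule: "those who screened positive were excluded". There is one exception, in South Africa, where repeat assessment was sometimes impossible: "adolescents who screened negative on the PHQ-A and GAD-7 during Phase 1 were considered eligible, without a repeat screening assessment before enrolment".
- **When baseline happens.** *Data collection for pilot cRCT* starts the adolescent baseline directly after the MMAPP screen and enrolment. The MMAPP is also the tool that yields the PHQ-A and GAD-7 scores at follow-up.
- **Delivery.** Sessions are given to groups, and trained facilitator pairs are each assigned to a school (*Interventions*; *Training and supervision of intervention facilitators*).

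**The concern.** The pilot exists partly to supply the parameters for sizing the full trial (*Sample size*). For a cluster trial the ICC is one of them, and it should be the ICC of the outcome on which that trial is powered. Here the named source is the one time point at which nobody can have that outcome, because entry selects on the same instrument and the same cut-offs.

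What remains at baseline is an ICC for something else, such as continuous symptom scores cut off from above. That figure also predates any clustering created by delivering the intervention in groups within schools. If it were carried into the sample size formula as though it belonged to cumulative incidence, the design effect of the full trial would rest on a quantity whose relation to the right one is unknown.

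**Working it through.** **1. The plan's own figure.** 8 schools × 30 = 240 per country, and 4 arms × 60 = 240, so the stated target is reproduced. The article gives no ICC, design effect, event rate or power, so every such value below is an assumption.

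**2. The outcome's ICC at baseline.** The one-way ANOVA estimator is

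ICC = (MSB − MSW) / (MSB + (m − 1) MSW),

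with m the number per school. If caseness is 0 for everyone, MSB = 0 and MSW = 0, giving 0/0. This holds for 8 schools of 30 and for 24 schools of 30. A few South African adolescents could be above a cut-off at T0 if their only screen was in Phase 1. They would be prevalent cases, not the planned incidence outcome.

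**3. Why the value matters.** The design effect is 1 + (m − 1) × ICC, with m = 30. For illustration, assume 30% vs 20% incidence, two-sided 5% and 80% power:

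n = [1.96 √(2 × 0.25 × 0.75) + 0.842 √(0.3 × 0.7 + 0.2 × 0.8)]² / 0.10² ≈ 294 per arm before clustering.

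| Assumed ICC | Design effect | n per arm | Schools of 30 per arm |
|---|---|---|---|
| 0.01 | 1.29 | 380 | 13 |
| 0.05 | 2.45 | 721 | 25 |
| 0.10 | 3.90 | 1147 | 39 |

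**4. The continuous-score ICC as a stand-in.** The simulation assumes normal scores, a population school ICC of 0.05, within-school retest correlation 0.6, two negative screens and then three follow-ups in the same cohort. Design effects are 1 + 29 × ICC from the rounded ICCs.

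| Screening negative | Baseline-score ICC | Cumulative-incidence ICC | Design effect, baseline score | Design effect, outcome |
|---|---|---|---|---|
| 50% | 0.015 | 0.014 | 1.44 | 1.41 |
| 70% | 0.020 | 0.015 | 1.58 | 1.44 |
| 85% | 0.028 | 0.014 | 1.81 | 1.41 |

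A repeat run gave 0.015 to 0.027 for the baseline score and 0.014 to 0.016 for cumulative incidence. Selection pulls the score ICC below 0.05. The outcome's ICC is also low, because the outcome is dichotomised and comes from the same selected adolescents.

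When extra school-level variance arising after baseline was added, the outcome ICC rose to 0.05 to 0.07. The design effect is then 1 + 29 × 0.05 = 2.45 to 1 + 29 × 0.07 = 3.03. Baseline contains no information on that variance, so it cannot separate the two situations.

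**5. What follow-up can deliver.** Assume 25% incidence and a true ICC of 0.05. The central 95% range of estimates is:

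| Schools | 30 followed per school | 24 followed per school (20% loss) |
|---|---|---|
| 8 (one country) | −0.01 to 0.15 | −0.02 to 0.16 |
| 24 (all) | 0.01 to 0.10 | 0.01 to 0.11 |

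These ranges ignore arm and country effects. Allowing for 12 arm-by-country cells leaves 24 − 12 = 12 degrees of freedom, so the real precision is lower. Colombia enrolled 160 adolescents, an average of 160 / 8 = 20 per school, which lowers it further.

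**The case against.** **No outcome is named for the ICC.** The sentence does not say the ICC will be computed on caseness, and a baseline ICC of continuous scores is estimable. This stands, and it means the analysis would not literally fail. It does not make baseline a source for the ICC of the outcome the full trial will be powered on.

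**Follow-up school variance may appear anyway.** The cross-country models carry random intercepts for schools and may include pooled outcome analyses. These are optional, and the ICC sentence is not tied to them. The country-specific models use fixed school effects, and cumulative incidence is handled only descriptively. A later analysis plan may add detail, but the article has already made a positive choice of source.

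**Baseline is cleaner.** It has no intervention effect to remove, whereas the follow-up ICC must be separated from arm effects with two schools per arm per country. The imprecision is real, and it argues for reporting an interval and using a range. It does not argue for substituting a different quantity.

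**A stronger reading that does not hold.** A reader might infer that the full trial would be under-sized by a stated amount. Setting design effects of 1.41 to 1.81 from truncated baseline scores against 2.45 for an ICC of 0.05 suggests 1 − 1.81/2.45 = 26% to 1 − 1.41/2.45 ≈ 42–43% too few participants. That compares unlike things: 0.05 is the ICC of a continuous score in an unselected population, while the planned outcome is binary and measured in the selected cohort. Under the same assumptions its ICC is about 0.014 to 0.016, no larger than the baseline-score ICC. Under-sizing appears only if clustering that arises after baseline is assumed.

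**Conclusion.** The point stands, at moderate severity. Under the article's own eligibility rule and outcome definition, the ICC of the planned primary outcome is not estimable from baseline data. The only gap in that statement is the possible handful of South African adolescents enrolled on a Phase 1 screen alone.

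A baseline-score ICC is computable but belongs to a different variable in a range-restricted, pre-delivery sample. Neither the size nor the direction of its error for cumulative incidence can be determined from baseline. In the simulations it ran from roughly equal to the outcome ICC, through somewhat above it, to well below it (0.05 to 0.07) once post-baseline school variance was assumed. All of these rest on assumed normal scores, retest correlation, screening rates and ICCs.

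The severity goes no higher because no feasibility outcome, progression criterion, randomisation step or assessment in the pilot depends on this sentence. It affects one input to a later trial.

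**What to change.** Reword the ICC sentence in *Sensitivity to change analyses on participants outcome data* to say that:

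- the school ICC of cumulative incidence, and of PHQ-A and GAD-7 scores at follow-up, will be estimated from T1 to T3, adjusted for arm and country, pooled over the 24 schools, and reported with a confidence interval;
- the baseline-score ICC and the caseness ICC from the Phase 1 survey (about 500 adolescents per country from the same schools, before selection on the cut-offs) will be reported as supporting evidence, noting that Phase 1 gives prevalence and not 18-month incidence;
- the full trial's sample size will be run over a range of ICCs informed by these estimates.

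The cost is a small change of wording and a short extra analysis. No data are needed beyond the assessments already planned. The drawback is an imprecise follow-up ICC, on about 12 degrees of freedom, so the full trial's size will have to be presented as a range.
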